| Scenario Version       | V2.0                                                                                                                                                                                                                                                                                                                                                                                                                                                                                                                                                                                                                       |
| Principle Investigator | [name]                                                                                                                                                                                                                                                                                                                                                                                                                                                                                                                                                                                                           |
| Bidding Center         | Fujian Medical University Union Hospital                                                                                                                                                                                                                                                                                                                                                                                                                                                                                                                                                                                   |
| Study Population       | Patients with locally advanced gastric cancer (cT2-4/N+M0)                                                                                                                                                                                                                                                                                                                                                                                                                                                                                                                                                                 |
| Purpose of Research    | To investigate the efficacy and safety of apatinib combined with S-1 plus oxaliplatin (SOX) as a neoadjuvant treatment for locally advanced gastric cancer.                                                                                                                                                                                                                                                                                                                                                                                                                                                                |
| Research Design        | Multicenter, single-arm, prospective                                                                                                                                                                                                                                                                                                                                                                                                                                                                                                                                                                                       |
| Case Grouping          | Single group                                                                                                                                                                                                                                                                                                                                                                                                                                                                                                                                                                                                               |
| Sample Size            | 50 cases                                                                                                                                                                                                                                                                                                                                                                                                                                                                                                                                                                                                                   |
| Inclusion Criteria     | 
 
● Age from 18 to 75 years
 
● Primary gastric adenocarcinoma (papillary, tubular, mucinous, signet ring cell, or poorly differentiated) confirmed pathologically by endoscopic biopsy
 
● cT2-4/N+M0 at preoperative evaluation according to the American Joint Committee on Cancer (AJCC) Cancer Staging Manual Seventh Edition
 
● No distant metastasis is observed. And the spleen, pancreas or other adjacent organs are not involved by the tumor.
 
● Performance status of 0 to 2 on Eastern Cooperative Oncology Group scale (ECOG)
 
 |

|                    |                                                                                                                                                                                                                                                                                                                                                                                                                                                                                                                                                                                                                                                                                                                                                                                                                                                                                                                                                                                                                    |
|--------------------|--------------------------------------------------------------------------------------------------------------------------------------------------------------------------------------------------------------------------------------------------------------------------------------------------------------------------------------------------------------------------------------------------------------------------------------------------------------------------------------------------------------------------------------------------------------------------------------------------------------------------------------------------------------------------------------------------------------------------------------------------------------------------------------------------------------------------------------------------------------------------------------------------------------------------------------------------------------------------------------------------------------------|
|                    | 
 
● Without previous surgery, chemotherapy, radiotherapy, immunotherapy, or targeted therapy for gastric cancer.
 
● Estimate life is equal or more than 3 months
 
● No serious heart, lung, liver dysfunction; no jaundice or obstruction of the digestive tract; no acute infection
 
● The main organ function is normal, and meet the following criteria:
 blood routine examination(No blood transfusion within 14 days)
 HB<math>\geq</math>100g/L,
 WBC<math>\geq</math>3.5<math>\times</math>10^9/L,
 ANC<math>\geq</math>1.5<math>\times</math>10^9/L,
 PLT<math>\geq</math>100<math>\times</math>10^9/L;
 blood biochemical examination
 BIL<1.5 ULN,
 ALT and AST<2.5ULN, GGT<math>\leq</math>1.5<math>\times</math>ULT;
 Cr<math>\leq</math>1ULN, creatinine clearance > 60ml/min (Cockcroft-Gault formula)
 
 
● Written informed consent
 
 |
| Exclusion Criteria | 
 
● Pregnant and lactating women
 
● Severe mental disorder
 
● History of previous upper abdominal surgery (except for laparoscopic cholecystectomy)
 
● History of previous chemotherapy or radiotherapy
 
● History of other malignant disease within the past 5 years
 
● History of unstable angina or myocardial infarction within the past 6 months
 
● History of cerebrovascular accident within the past 6 months
 
● History of continuous systematic administration of corticosteroids within 1 month
 
                                                                                                                                                                                                                                                                                                                                                                                                 |

|                                 |                                                                                                                                                                                                                                                                                                                                                                                                                                                                                                                                                                                                                                                                                                                   |
|---------------------------------|-------------------------------------------------------------------------------------------------------------------------------------------------------------------------------------------------------------------------------------------------------------------------------------------------------------------------------------------------------------------------------------------------------------------------------------------------------------------------------------------------------------------------------------------------------------------------------------------------------------------------------------------------------------------------------------------------------------------|
|                                 | 
 
● Emergency surgery due to complication (bleeding, obstruction or perforation) caused by gastric cancer
 
● Patients with a clear tendency of gastrointestinal bleeding, such as: active ulceration, fecal occult blood test(++). History of hematemesis and melena within 2 months, coagulation disorders (INR>1.5、APTT>1.5 ULN).
 
● Positive urinary protein (uric albumen check(++), or 24-hour urinary protein content>1.0g)
 
● Factors affecting oral administration, such as dysphagia, uncontrollable nausea and vomiting, chronic diarrhea, and intestinal obstruction
 
● Drug allergy to experimental medicine
 
 |
| Rejection Criteria              | 
 
● Do not meet the inclusion criteria and meet the exclusion criteria;
 
● Simultaneous application of CFDA-approved modern Chinese medicine or immunomodulators for the treatment of gastric cancer;
 
● Radiation therapy or other local treatments during the study periods;
 
● Incomplete data;
 
● Do not take medicine according to the dosage, method, and treatment prescribed in the protocol.
 
                                                                                                                                                                                                                             |
| Criteria for Stopping Treatment | 
 
● Receiving surgery;
 
● Disease progression;
 
● Unbearable toxicity after dose reductions;
 
● Patient refusal;
 
● Investigator decision that stopping treatment was in the best interest of the patient;
 
● Death.
 
                                                                                                                                                                                                                                                                                                                                                                                                      |
| Intervention                    | 
 
● Oxaliplatin, 130 mg/m^2 intravenously on day 1;
 
● Apatinib, 500 mg orally once daily on days 1 to 21;
 
● S-1 (Tigio), 40-60 mg orally twice daily on days 1 to 14.
 
 
The dose of S-1 is based on body surface area (BSE):
                                                                                                                                                                                                                                                                                                                                                                                                     |

|                  |                                                                                                                                                                                                                                                                                                                                                                                                                                                                                                                                                                                                                                                                                                 |                                        |             |
|------------------|-------------------------------------------------------------------------------------------------------------------------------------------------------------------------------------------------------------------------------------------------------------------------------------------------------------------------------------------------------------------------------------------------------------------------------------------------------------------------------------------------------------------------------------------------------------------------------------------------------------------------------------------------------------------------------------------------|----------------------------------------|-------------|
|                  | ●                                                                                                                                                                                                                                                                                                                                                                                                                                                                                                                                                                                                                                                                                               | BSE                                    | Dose        |
|                  |                                                                                                                                                                                                                                                                                                                                                                                                                                                                                                                                                                                                                                                                                                 | < 1.25m                    | 40mg× 2/day |
|                  |                                                                                                                                                                                                                                                                                                                                                                                                                                                                                                                                                                                                                                                                                                 | 1.25m  - 1.5m  | 50mg× 2/day |
|                  |                                                                                                                                                                                                                                                                                                                                                                                                                                                                                                                                                                                                                                                                                                 | > 1.5m                     | 60mg× 2/day |
|                  |                                                                                                                                                                                                                                                                                                                                                                                                                                                                                                                                                                                                                                                                                                 |                                        |             |
| Outcome Measures | 
Primary Outcome Measures :
 
 
● R0 resection rate
 
 
Secondary Outcome Measures :
 
 
● Pathological response rate
 
● Radiologic response rate
 
● Surgical safety: including surgical mortality, surgical morbidity (bleeding, anastomotic leakage, wound infection), reoperation rate, length of stay, etc.
 
● Drug safety: including adverse events (AEs), severe adverse events (SAEs), and drug-related AEs (like hypertension, hand-foot syndrome, and proteinuria).
 
● Disease-free survival (DFS)
 
● Overall survival (OS)
 
 |                                        |             |

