## Flow Chart

| Items                     | Screening Period                 |                                  | Neoadjuvant Treatment Period |            |            |            |                         |            |            |            |            | Surgery                       |                              | Adjuvant Treatment Period |            |            |
|---------------------------|----------------------------------|----------------------------------|------------------------------|------------|------------|------------|-------------------------|------------|------------|------------|------------|-------------------------------|------------------------------|---------------------------|------------|------------|
|                           | Within 2 weeks before enrollment | Within 1 weeks before enrollment | Cycle 1                      | Cycle 2    |            | Cycle 3    |                         | Cycle 4    |            | Cycle 5    |            | Within 1 weeks before surgery | Within 1 weeks after surgery | Cycle 1                   |            | Cycles 2-6 |
|                           |                                  |                                  | Day 7 (±3)                   | Day 1 (±3) | Day 7 (±3) | Day 1 (±3) | Day 7 (±3)  | Day 1 (±3) | Day 7 (±3) | Day 1 (±3) | Day 7 (±3) |                               |                              | Day 1 (±3)                | Day 7 (±3) | Day 1 (±3) |
| Baseline characters       |                                  |                                  |                              |            |            |            |                         |            |            |            |            |                               |                              |                           |            |            |
| Informed consent          | x                                |                                  |                              |            |            |            |                         |            |            |            |            |                               |                              |                           |            |            |

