| Pregnancy tests                  |   | x |                     |   |   |   |   |   |   |   |   |   |   |   |   |   |
| Radiologic assessments           |   |   |                     |   |   |   |   |   |   |   |   |   |   |   |   |   |
| Imaging examination † | x |   | Every 2 cycles (±7) |   |   |   |   |   |   |   |   |   |   |   |   | x |
| Other assessments                |   |   |                     |   |   |   |   |   |   |   |   |   |   |   |   |   |
| ECOG score                       |   | x |                     | x |   | x |   | x |   | x |   | x | x | x |   | x |
| Blood pressure monitoring        |   | x | x                   | x | x | x | x | x | x | x | x | x | x | x | x | x |
| Adverse events                   |   |   | x                   | x | x | x | x | x | x | x | x | x | x | x | x | x |
| Others                           |   |   |                     |   |   |   |   |   |   |   |   |   |   |   |   |   |
| Concomitant drugs                |   |   | x                   | x | x | x | x | x | x | x | x | x | x | x | x | x |
| Drug compliance                  |   |   |                     | x |   | x |   | x |   | x |   |   |   | x |   | x |

23 **Abbreviations**

| Abbreviations | Full names                                                    |
|----------------------|----------------------------------------------------------------------|
| AE                   | Adverse events                                                       |
| AGC                  | Advanced gastric cancer                                              |
| AKP                  | Alkaline phosphatase                                                 |
| ALB                  | Albumin                                                              |
| ALT                  | Alanine aminotransferase                                             |
| ANC                  | Absolute neutrophil count                                            |
| APTT                 | Activated partial thromboplastin time                                |
| AST                  | Aspartate aminotransferase                                           |
| Bid                  | Bis in die                                                           |
| BIL                  | Bilirubin                                                            |
| BSE                  | Body surface area                                                    |

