### 3.2.3 Rejection criteria

(1) Do not meet the inclusion criteria and meets the exclusion criteria;

(2) Simultaneous application of CFDA-approved modern Chinese medicine or immunomodulators for the treatment of gastric cancer;

(3) Radiation therapy or other local treatments during the study periods;

(4) Incomplete data;

(5) Do not take medicine according to the dosage, method, and treatment prescribed in the protocol.

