### 3.2.4 Criteria for Stopping Treatment

(1) Disease progression;

(2) Unbearable toxicity after dose reductions;

(3) Patient refusal;

(4) Investigator decision that stopping treatment was in the best interest of the patient;

(5) Death.

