#### **4.2 Neoadjuvant Treatment Period**

Intervention group: All enrolled patients receive 2-5 preoperative cycles of apatinib (500 mg orally once daily on days 1 to 21 and discontinued in the last cycle) plus SOX (S-1, 40-60 mg orally twice daily on days 1 to 14; oxaliplatin, 130 mg/m^2 intravenously on day 1) every 3 weeks.

- During neoadjuvant treatment, physical examination, ECOG PS assessment, tumor markers, and electrocardiograms are performed on day

1 of cycles 2, 3, 4, and 5. If cardiac pains or palpitations occur, myocardial enzyme spectrum (creatin kinase, lactate dehydrogenase), electrocardiogram, and cardiac ultrasound should be immediately performed;

- Peripheral blood routine and blood chemistry are performed on day 7 of cycle 1 and days 1, 7 of cycles 2, 3, 4, and 5;
- Urinary routine, stool routine, and coagulation tests are performed on day 1 of cycles 2, 3, 4, and 5;
- Imaging examination should be performed under the same conditions (layer thickness of scanning, use of contrast agent, etc.) as possible. The lesions detected at the baseline should be followed up every 2 cycles;
- Discomforts during the treatment should be recorded and graded according to the the NCI-CTCAE, version 4.0. If necessary, develop the treatment plan with the department of oncology, and record the reasons for dose adjustment or delay, supportive treatment, and outcomes in the CRF;
- Blood pressure monitoring is performed by the patient himself/herself and recorded in a diary card. Measurement should be done at least 3 times a week during the first 2 cycles. If abnormal, the blood pressure should be monitored daily; otherwise the blood pressure is measured weekly after 2 cycles. At each visit, researchers should measure the blood pressure again. Before measurement, smoking and coffee are not permitted. Take a sitting position. The elbows should be placed at the same level as the heart, and each measurement should be taken on the same side.

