#### 4.4 Adjuvant treatment period

Intervention group: All enrolled patients receive 6 postoperative cycles of apatinib (500 mg orally once daily on days 1 to 21) plus SOX (S-1, 40-60 mg orally twice daily on days 1 to 14; oxaliplatin, 130 mg/m^2 intravenously on day 1) every 3 weeks.

- During adjuvant treatment, peripheral blood routine and blood chemistry are performed on days 1, 7 of cycle 1 and day 1 of cycles 2, 3, 4, 5, and 6;
- Physical examination, ECOG PS assessment, tumor markers, and electrocardiograms are performed on day 1 of each cycle;
- Imaging examination should be performed under the same conditions (layer thickness of scanning, use of contrast agent, etc.) every 3 cycles;
- Discomforts during the treatment should be recorded and graded according to the NCI-CTCAE, version 4.0. If necessary, develop the treatment plan with the department of oncology, and record the reasons for dose adjustment or delay, supportive treatment, and outcomes in the CRF;
- Blood pressure monitoring is performed by the patient himself/herself and recorded in the diary card. Measurement should be done at least 3 times a week during the first 2 cycles. If abnormal, the blood pressure should be monitored daily; otherwise the blood pressure is measured weekly after 2 cycles. At each visit, researchers will measure the blood pressure again. Before measurement, smoking and coffee are not permitted. Take a sitting position. The elbows should be placed at the same level as the heart, and each measurement should be taken on the same side.

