## **6.2 Definitions of Analysis Sets**

Full Analysis Set (FAS): included patients who receive at least one cycle of neoadjuvant treatment.

Per-protocol Set (PPS): included patients who comply with the study protocol, have good compliance, do not take prohibited drugs during the treatment, receive surgery, and complete the CRF. Analysis of the efficacy should be performed in both FAS and PPS populations.

Safety Analysis Set (SAS): included patients who receive at least one cycle of neoadjuvant treatment and have safety records.

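### The synopsis lists surgery as a reason to stop treatment without limiting it to the neoadjuvant phase, which conflicts with 3.2.4 and with the six postoperative cycles in 4.4 and the flow chart

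*Protocol*

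**What the plan says.** The synopsis row Criteria for Stopping Treatment has six entries. The first is "Receiving surgery", with no phase attached. The other five are progression, intolerable toxicity, refusal, the investigator's decision and death. Section 3.2.4 carries the same title, starts at "1) Disease progression", and contains those five entries but not surgery.

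Treatment before surgery is set in 4.2: "All enrolled patients receive 2-5 preoperative cycles of apatinib", with SOX. Treatment after surgery is set in 4.4: "All enrolled patients receive 6 postoperative cycles of apatinib", again with SOX, in three-week cycles. The flow chart places an "Adjuvant Treatment Period" after the surgery columns, with cycle 1 and cycles 2 to 6, and its "Drug compliance" row is marked on day 1 of each of these cycles.

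The synopsis row Intervention gives doses and dosing days only. It names no phase and no number of cycles, and the protocol does not say whether the synopsis or the body prevails.

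Two further provisions bear on the consequences. Section 6.2 (Definitions of Analysis Sets) defines the per-protocol set (PPS) as "included patients who comply with the study protocol, have good compliance, do not take prohibited drugs during the treatment, receive surgery", plus a completed case report form, and asks for efficacy analyses in both the full analysis set (FAS) and the PPS. Section 3.2.3 lists among its rejection criteria "Do not take medicine according to the dosage, method, and treatment prescribed in the protocol".

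**The concern.** A patient cannot both stop treatment on having surgery and receive six cycles afterwards. The synopsis rule, as worded, applies to every patient who is operated on, which is the intended course for everyone in the trial.

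Two things are at stake. The first is postoperative treatment itself. In a multicentre trial, sites that read the rule differently would give different adjuvant exposure, and that exposure lies behind disease-free and overall survival, both secondary outcomes in the synopsis. The second is the meaning of compliance. The PPS requires surgery and adherence to the protocol, so every PPS candidate meets the synopsis stopping entry. The protocol then gives two answers to the question of what an adherent patient does next.

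**Working it through.** The protocol states no statistical figure on this point, so there is none to reproduce. The check is a comparison of the provisions, followed by simple counts.

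**1. The provisions side by side**

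| Place | Surgery stops treatment? | Treatment after surgery? |
|---|---|---|
| Synopsis, Criteria for Stopping Treatment | Yes, no phase given | Not mentioned |
| Synopsis, Intervention | Not mentioned | Not mentioned; doses and days only |
| 3.2.4 | Not listed | Not mentioned |
| 4.4 | Not mentioned | Six cycles |
| Flow chart | Not mentioned | Cycle 1 and cycles 2 to 6 |

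The synopsis entry stands alone. Section 3.2.4 does not contradict 4.4, and 4.4 agrees with the flow chart.

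**2. Cycles affected under a literal reading**

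- Preoperative cycles: 2 to 5 (4.2). Postoperative cycles: 6 (4.4).
- Planned total: 2 + 6 = 8 to 5 + 6 = 11.
- Share removed if treatment ends at surgery: 6/11 = 54.5% to 6/8 = 75%.

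**3. Compliance checks affected (flow chart)**

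- Before surgery, checks fall on day 1 of cycle 2 onwards: 1 check for 2 cycles, 4 checks for 5 cycles.
- After surgery: 6 checks. Total: 7 to 10.
- Share after surgery: 6/10 = 60% to 6/7 = 86%.
- The check on day 1 of adjuvant cycle 1 may look back to the last preoperative cycle. Without it: 5/10 = 50% to 5/7 = 71%.

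**4. Shift in the last-dose date under a literal reading**

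- Under 4.4 the last dose is apatinib on day 21 of adjuvant cycle 6: 5 × 21 + 20 = 125 days after adjuvant day 1. The gap from surgery to adjuvant day 1 is not stated; it is taken as 0, so the result is a lower bound.
- Under the synopsis the last dose precedes surgery. Section 4.3 puts surgery 2 to 4 weeks after neoadjuvant treatment. If that runs from the last dose, the last dose falls 14 to 28 days before surgery.
- Shift: 125 + 14 = 139 days (19.9 weeks) to 125 + 28 = 153 days (21.9 weeks).
- Section 4.2 drops apatinib in the last preoperative cycle, so the last drug given there is S-1 on day 14. If the 2 to 4 weeks run from the end of that 21-day cycle, add 7 days: 146 to 160 days (20.9 to 22.9 weeks).

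The End Date (3.4) and the start of follow-up (4.5) both run from the last dose, so they would move by the same amount. The figures in steps 2 to 4 apply only at a site that follows the synopsis against 4.4.

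**5. Primary endpoint**

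R0 status is fixed at surgery. FAS membership depends on at least one cycle of neoadjuvant treatment (6.2). Neither depends on what is given afterwards, so the R0 rate in the FAS does not change. PPS membership does depend on compliance, so the R0 rate in the PPS could change if patients were excluded on one reading and kept on the other. The protocol gives no basis for putting a number on that.

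**The case against.** The strongest reply is that the literal reading is implausible. The stated purpose is to study the combination as neoadjuvant treatment, and the synopsis mentions no adjuvant cycles. The other five entries are failure, withdrawal or death, whereas surgery is the goal of the neoadjuvant course. A rule that ends all study treatment for every patient who reaches that goal makes little sense. The flow chart and 4.2 to 4.4 also treat the neoadjuvant, surgical and adjuvant periods as separate, so ending one need not bar the next. As a guess at intent this stands, and most investigators would probably follow 4.4. It does not remove the conflict. No other entry in the row is phase-specific, the row does not mark this one as such, and 3.2.4 omits it.

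Several stronger conclusions might be inferred, and the protocol does not support them:

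- *A patient who stops at surgery must be rejected for not taking the drugs as prescribed (3.2.3).* That patient has stopped under a listed criterion, and nothing says that such a stop is non-compliance. The status is unclear rather than clearly a violation.
- *The last-dose date, End Date and start of follow-up become ambiguous.* Both dates run from the last drug actually given, which is observed for each patient. They would come earlier under a literal reading, but they remain determinate.
- *The primary endpoint is affected, or is wholly untouched.* Neither is right as a general statement. The FAS result is unaffected; the PPS result depends on how compliance is judged.
- *Surgical complications would go unrecorded.* Section 4.3 requires them to be recorded on either reading.

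**Conclusion.** The point holds as a minor internal inconsistency in an operational rule that is wrong as written. The synopsis entry conflicts with 3.2.4, 4.4 and the flow chart. Its literal effect would be the loss of all six adjuvant cycles and a last dose at least about 20 to 22 weeks earlier for a patient who would otherwise complete treatment. That size is conditional. It assumes that a site follows the synopsis literally, that no time passes between surgery and the first adjuvant dose, and that the 2 to 4 weeks in 4.3 run from the last neoadjuvant dose. It measures what the wording permits and does not predict what sites will do.

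The consequence that does not depend on site behaviour is narrower: the protocol does not settle whether stopping or continuing after surgery is the compliant course for the PPS. Confidence is high in the mismatch of the text and lower in any practical effect.

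**What to change.** Delete the surgery entry from the synopsis stopping list so that it matches 3.2.4. Alternatively, reword it as *surgery (ends neoadjuvant treatment only; adjuvant treatment per 4.4)*. Either version makes the six postoperative cycles the single rule and lets PPS compliance after surgery be judged against 4.4.

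The cost is a one-line wording amendment, handled through the usual protocol revision and ethics submission. Data collection, sample size and analysis do not change.
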